## 6. STUDY PROCEDURES

### 6.1 Schedule of Evaluations

| Assessment                             | Screening:
Baseline
prescribing
(Month -17
to Month 0) | Baseline,
Enrollment,
Randomization:
(Day 1) | Intervention
start (Month
1) | Continuously
Measured or
monitored | Intervention
end: (Month
18) | Follow-up
period:
(Month 19 to
Month 30) |
|----------------------------------------|--------------------------------------------------------------------|-------------------------------------------------------|------------------------------------|------------------------------------------|------------------------------------|---------------------------------------------------|
| Clinician-level
Assessments |                                                                    |                                                       |                                    |                                          |                                    |                                                   |
| Informed Consent Form                  |                                                                    | X                                                     |                                    |                                          |                                    |                                                   |
| Demographics                           |                                                                    | X                                                     |                                    |                                          |                                    |                                                   |
| Inclusion/Exclusion
Criteria        | X                                                                  | X                                                     |                                    |                                          |                                    |                                                   |
| Provider Attitudes
Survey           |                                                                    | X                                                     |                                    |                                          | X                                  |                                                   |
| Visit-level assessments         |                                                                    |                                                       |                                    |                                          |                                    |                                                   |
| ICD-9 codes                            | X                                                                  | X                                                     | X                                  | X                                        | X                                  | X                                                 |
| Ordering Data                          | X                                                                  | X                                                     | X                                  | X                                        | X                                  | X                                                 |
| Adverse Events                         |                                                                    |                                                       | X                                  | X                                        | X                                  |                                                   |

## 6.2 Description of Evaluations

### 6.2.1 Screening Evaluation

#### Consenting Procedure

With the assistance of each site's medical director, we will send providers at participating sites an introductory email that includes a description of the broad goals of the study, a general description of the intervention, and a link to the electronic consent form and baseline survey. The consent document will indicate that participation is voluntary and that decisions to participate (or not) will have no bearing on any provider's status at his or her clinic. Providers who provide consent to participate will be asked to complete an online survey and brief educational session prior to the intervention phase, permit de-identified patient records pertaining to patients who saw them for ARIs to be included in the study database, and complete a 15 minute post-intervention survey. We will also describe compensation that providers will receive for participation. We will send up to 6 follow up emails to providers who do not respond, and study personnel will contact them in person when feasible.

### 6.2.2 Enrollment, Baseline, and/or Randomization

#### Enrollment

Enrollment date will be documented on the online consent form at the time of consent. Interventions will be initiated after all clinicians in a practice have been enrolled or declined to participate.

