### **3. STUDY DESIGN**

The Use of Behavioral Economics and Social Psychology to Improve Treatment of Acute Respiratory Infections (BEARI) Trial is a multisite, cluster-randomized controlled trial with practice as the unit of randomization. The primary aim is to test the ability of three interventions based on behavioral economic principles to reduce the rate of inappropriate antibiotic prescribing for ARIs. We will randomize practices in a 2 x 2 x 2 factorial design to receive up to three interventions for non-antibiotic-appropriate diagnoses: 1) Accountable Justifications: When prescribing an antibiotic for an ARI, clinicians are prompted to record an explicit justification that appears in the patient electronic health record ; 2) Suggested Alternatives: Through computerized clinical decision support, clinicians prescribing an antibiotic for an ARI receive a list of non-antibiotic treatment choices (including prescription options) prior to completing the antibiotic prescription; and 3) Peer Comparison: Each provider’s rate of inappropriate antibiotic prescribing relative to top-performing peers will be reported back to the provider periodically by email. We will enroll approximately 300 clinicians (practicing attending physicians or advanced practice nurses) from 49 participating outpatient clinic sites and collect baseline data. All participating clinicians will receive a brief educational module reviewing ARI treatment guidelines at the time of consent and enrollment. Surveys will be administered at the time of enrollment and after the intervention is complete. The primary outcome is the antibiotic prescribing rate for office visits with non-antibiotic-appropriate ARI diagnoses. Secondary outcomes will examine antibiotic prescribing more broadly. The 18- month intervention period will be followed by a one year follow-up period to measure persistence of effects after interventions cease. Data from electronic medical records for participating practices are transferred to the Data Coordinating Center on a weekly basis.

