### **4.3 Study Enrollment Procedures**

All clinicians with adult patients in participating practices will be contacted by email and in-person meetings. Enrollment and consent will be conducted using an online survey administration application.

The email includes a description of the broad goals of the study, a general description of the intervention, compensation providers would receive for participation, and a link to the electronic consent form and baseline survey.

The baseline survey includes an educational module. After providing consent, providers are asked to complete a 15 to 20 minute online survey and educational module. The educational module contains information about ARIs derived from evidence based guidelines and systematic reviews. The educational module also describes the interventions to which a clinician's site was assigned,

including changes they would observe in their EHR (for Accountable Justifications and Suggested Alternatives interventions) and examples of the kinds of emails they would receive (Peer Comparison). These examples include Appendix B: Example of Suggested Alternatives Order Set and Appendix C: Sample Peer Comparison Email Text.

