## **5. STUDY INTERVENTIONS**

### **5.1 Interventions, Administration, and Duration**

The intervention period will be 18-months in length for all participants, with a one year follow-up period to measure persistence of effects after interventions end. The pre-intervention baseline period will be 6 months in length.

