## **9. STATISTICAL CONSIDERATIONS**

### **9.1 General Design Issues**

#### *Hypotheses*

Our primary hypothesis is that practices randomized to receive behavioral economic interventions will have decreases over time in antibiotic prescribing rates for non-antibiotic appropriate ARIs, compared to contemporaneous antibiotic prescribing rates for non-antibiotic appropriate ARIs among control practices. This hypothesis will be evaluated in an intent-to-treat difference-in-differences framework using a mixed-effects logistic regression model. Fixed effects will include the effects of interventions over time (i.e., interactions between randomization assignment and time), using a 6-months prior to the intervention baseline period. Providers and randomization unit (clinic) will be modeled as random effects.

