### Additional statements (for PC+ subjects)

*[Injunctive norm] These guidelines for treating non-specific URIs have been endorsed by the American Academy of Family Physicians, the American College of Physicians, the Infectious Diseases Society of America, and the Centers for Disease Control and Prevention.*

Response task additions (for PC+ subjects)

- None (same as PC-)

Intervention summary (for PC+ subjects)

- During the study, you will receive regular updates on your own rate of antibiotic prescribing for patients who have non-specific URIs. As a demonstration of achievable performance, these updates will also include the antibiotic prescribing rate achieved by the 10% of physicians in [name of clinic] whose prescribing is most guideline-concordant.

Additional statements (for AJ+ subjects)

*[Importance of justification] Guidelines are intended to help clinicians treat the majority of their patients. However, there can be clinical reasons why a guideline might not apply to a particular patient. When there is a good clinical reason, a physician might justifiably choose not to follow a guideline.*

*If a physician decides that there is a clinically justifiable reason to prescribe antibiotics to a patient with a non-specific URI, he or she should have a clear sense of what this reason is. He or she should be able to state the justification for not following the guideline.*

Response task additions (for AJ+ subjects)

- To what extent do you agree with these overall guidelines for treating non-specific URIs? [completely agree to completely disagree]
- To what extent do you agree that antibiotics are not indicated for the treatment of non-specific URIs? [completely agree to completely disagree]
- (Other response tasks same as AJ-)...

Intervention summary (for AJ+ subjects)

- During the study, if you prescribe antibiotics to patient who you are seeing for a non-specific URI, you will be asked to supply a brief written justification for prescribing antibiotics. The justification that you write will be entered in the patient's medical record. If you do not write a justification, the phrase "No justification for prescribing antibiotics was given" will appear in your encounter note.

Additional statements (for SA+ subjects)

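### The six-month baseline can include visits made after clinicians saw arm-specific content at consent; if that content lowers prescribing, the primary contrast is pulled toward no effect

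*Protocol*

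**What the plan says.** **Baseline window.** Section 5.1 states: "The pre-intervention baseline period will be 6 months in length". Section 9.1 (Hypotheses) specifies the difference-in-differences model "using a 6-months prior to the intervention baseline period". The time terms in section 9.5 are baseline and intervention months 0-6, 7-12 and 13-18, with nothing between baseline and month 0.

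**Timing of the module.** Section 3: "All participating clinicians will receive a brief educational module reviewing ARI treatment guidelines at the time of consent and enrollment". Section 6.2.1 (Consenting Procedure) also has clinicians complete a "brief educational session prior to the intervention phase".

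**Content of the module.** A sentence in section 4.3 begins "The educational module also describes the interventions to which a" and goes on to refer to the clinician's own site. Appendix A gives the arm-specific text. Peer Comparison clinicians read an endorsement labelled as an injunctive norm, starting "These guidelines for treating non-specific URIs have been endorsed by the American Academy of Family Physicians". Accountable Justification clinicians read about being able to justify departures from the guideline, and learn that a missing justification will be recorded. Suggested Alternatives clinicians are reminded of non-antibiotic options. Similar blocks are repeated for sinusitis, pharyngitis and bronchitis.

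**Launch.** Section 6.2.2: "Interventions will be initiated after all clinicians in a practice have been enrolled or declined to participate". Section 6.2.1 describes recruitment as a process: "We will send up to 6 follow up emails to providers who do not respond", with in-person contact when feasible.

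**Schedule.** The table in section 6.1 shows baseline prescribing from Month -17 to Month 0, then enrolment and randomization on Day 1, then intervention start in Month 1.

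**The concern.** In a difference-in-differences analysis the baseline should be free of anything that differs by arm. Here every clinician except the last to answer in a practice waits between consent and launch, and during that wait has already read material that depends on the assigned arm. Section 2.2 counts some of that material among the interventions' mechanisms: injunctive norms for Accountable Justification and Peer Comparison, and making alternatives more salient for Suggested Alternatives.

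If that material changes prescribing, the baseline rate moves in the intervention clinics only, and part of the effect is subtracted from itself. The affected quantity is the intervention-by-period term, which carries the primary hypothesis.

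**Working it through.** **Step 1: does the stated rule put post-consent visits into baseline?** Sections 5.1 and 9.1 set the baseline as the six months before the intervention. Section 6.2.2 starts the intervention only once the whole practice has been resolved. Sections 3 and 6.2.1 place the module at consent, before the intervention phase. Section 9.5 has no transition term, and no section excludes visits between consent and launch. Read together, these visits are baseline visits.

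**Step 2: does the schedule table settle it?** It does not. Month -17 to Month 0 is 18 months, not the 6 in sections 5.1 and 9.1. Its single Day 1 for enrolment does not fit a process of repeated emails and visits with launch waiting on the last clinician. If the table's order held literally, no baseline visit would follow the module and the bias would be zero.

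**Step 3: size of the bias.** Let Δ be the true effect in percentage points, p the untreated rate, and d the reduction caused by the arm-specific content before launch. Let g be the mean number of months, over all clinicians, between consent and launch that fall inside the six-month baseline. Assume visits are spread evenly.

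- Intervention baseline: p − (g/6) × d
- Intervention period: p − Δ
- Change in intervention clinics: −Δ + (g/6) × d
- Change in control clinics: 0, apart from any shared trend
- Contrast: −[Δ − (g/6) × d], so the loss is (g/6) × d

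In the 2 × 2 × 2 design this applies factor by factor. Content for one factor biases that factor's contrast; content for the other two is roughly balanced across it.

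Section 9.2 plans for Δ = 7 points. The protocol gives neither g nor d, so the values below are assumptions.

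| g (months) | d (points) | Loss = (g/6) × d | Contrast left of 7 | Share lost |
|---|---|---|---|---|
| 0 | any | 0 | 7.00 | 0% |
| 1 | 1 | 1/6 × 1 = 0.17 | 6.83 | 2% |
| 2 | 2 | 2/6 × 2 = 0.67 | 6.33 | 10% |
| 3 | 3.5 | 3/6 × 3.5 = 1.75 | 5.25 | 25% |

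The last row assumes a three-month mean gap and pre-launch text alone delivering half the planned effect. If the step from Day 1 to Month 1 in the schedule is read as a gap of at most one month, g cannot exceed 1 and the loss cannot exceed d/6.

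**Step 4: the general module.** Let e be its effect in every arm, with mean gaps g₁ in intervention clinics and g₀ in control clinics. Its contribution to the contrast is (g₁ − g₀)/6 × e, which is zero when the gaps are equal. One enrolment process applies to all randomized practices, and nothing in the protocol suggests that gaps differ by arm.

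**The case against.** The strongest reply is that a contaminated baseline is inferred rather than stated. The schedule ends baseline before Day 1, section 5.1 gives a length without saying that the window abuts launch, and no duration is given for enrolment, which might take only weeks. Exact window dates are also often left to a statistical analysis plan. This stands in part: the gap may be short and the bias negligible. However, the protocol itself fixes the window in section 9.1 and contradicts it in section 6.1, so this is not merely detail left for later.

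A reader might infer that the baseline is already treated. The documents do not support that. Before launch no alert, order set or email is active, only visits after consent are exposed, and the pre-launch content is a few passages in one online session of 15 to 20 minutes. Section 2.1 itself doubts that education does much.

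A reader might also infer that bias toward no effect is established. It is conditional. The Accountable Justification text grants that departing from a guideline can be justified, which could plausibly raise prescribing and reverse the sign.

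A large loss is a further tempting reading. For example, g = 4 and d = 3 would cost 2.0 points, or 29% of 7. That needs a four-month mean gap and text alone producing 43% of the planned effect, and nothing in the protocol points to either.

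Finally, the comparison with clinicians' own historical rates in the Précis should not be counted as affected, because the Précis does not say that those rates come from this six-month window.

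**Conclusion.** The point holds in conditional form. As written, the baseline can include visits made after a clinician has seen content specific to the assigned arm, and no rule removes them. If that content lowers prescribing, the primary contrast is attenuated by about (g/6) × d points.

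Under modest assumptions the loss is 0.17 to 0.67 of the planned 7 points; it is nil if the baseline in practice closes before first consent. These figures assume even visit volume and values of g and d that the documents do not supply. The general module is not a material source of bias between arms.

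Separately, and without any assumption, the schedule conflicts with sections 5.1 and 9.1 on the length of baseline, and with sections 6.2.1 and 6.2.2 on enrolment as a process. The point is worth correcting because it touches the primary contrast and the remedy is cheap, not because a large bias has been shown.

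**What to change.** In sections 5.1, 9.1 and 9.5, define each practice's six-month baseline to end on the day before the first consent in that practice, which is when an assignment is first disclosed there. Treat visits from that date until launch as a transition period, excluded from both baseline and intervention. Amend the schedule in section 6.1 to show a six-month analysis baseline within the longer data-collection window, enrolment as a period, and the transition before launch.

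This needs no new data: section 6.2.2 already records enrolment dates, and the schedule already collects diagnosis and ordering data from Month -17. Starting the cut-off at the first recruitment email is unnecessary, since sections 4.3 and 6.2.1 describe that email as giving only broad goals and a general description. The cost is a change of wording, a baseline that sits slightly further from launch, and the loss of the transition visits from the analysis.

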### 9.5 Data Analyses

We will use the following descriptive statistics to characterize the sample: Means and medians for continuous measures, frequencies for count data, standard deviations and interquartile ranges for variance.

For inferential analysis of our hypotheses, we will employ a mixed-effects hierarchical logistic regression model to estimate the adjusted marginal effect over time of each intervention on the primary outcome using. Fixed effects will include intervention assignment, time period dummy variables (the baseline prescribing rate for each clinician, the intervention and intervention months 0-6, 7-12, and 13-18), and time period interacted with intervention assignment. Providers and randomization unit (clinic) will be included as random effects. To isolate the effect of each individual intervention (Suggested Alternatives, Accountable Justification, or Peer Comparison) on the primary outcome, controlling for any co-occurring interventions under the factorial design.

To assess diagnostic drift, we will use the same analytic model as for the primary outcome, but with the percentage of *all* ARIs that is coded as antibiotic-appropriate in each study arm as the dependent variable (a secondary outcome).

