| Alerts reappear if bypassed?                                                                                               | Alerts appear for all antibiotic prescriptions at which point clinician indicates it is for an ARI. | Upon encounter sign out if antibiotic has been ordered.                                            | Upon encounter sign out if antibiotic has been ordered.                                                                  |
| Development and testing                                                                                                    | 5 months                                                                                            | 7 months                                                                                           | 10 months                                                                                                                |

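### The protocol gives no common launch date and the primary model has no calendar-time term, so the comparison with contemporaneous controls is not secured if practices start at different times of year

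*Protocol*

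**What the plan says.** **Start of the interventions.** Protocol section 6.2.2 (Enrollment) sets the condition practice by practice: "Interventions will be initiated after all clinicians in a practice have been enrolled or declined to participate". No calendar launch date is given for the trial, an organization or an arm. The schedule in section 6.1 counts relative months only.

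**Time in the model.** Besides the assigned intervention itself, section 9.5 describes its time terms as "time period dummy variables (the baseline prescribing rate for each clinician, the intervention and intervention months 0-6, 7-12, and 13-18". The effects of interest come from a further fixed effect, which it calls "time period interacted with intervention assignment". On clustering, the same section says: "Providers and randomization unit (clinic) will be included as random effects". Neither 9.1 nor 9.5 lists a calendar-month, season or calendar-time term, or a clinic-by-period random effect.

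**The comparison promised.** Section 9.1 describes a difference-in-differences in which intervention practices are "compared to contemporaneous antibiotic prescribing rates for non-antibiotic appropriate ARIs among control practices".

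**Length of the baseline.** Section 5.1: "The pre-intervention baseline period will be 6 months in length". That is half a seasonal cycle.

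**Build times.** Appendix C, in the row "Development and testing", gives 5, 7 and 10 months for the three EHR systems.

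**The concern.** A difference-in-differences removes season when period k covers the same calendar months in every practice. If month 0 is the practice's own start date, practices starting in different months contribute different seasons to the baseline and to each later period. The period indicators then no longer describe a shared time effect, and nothing else in the model ties visits to the calendar.

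The six-month baseline sharpens this. Months 0-6 and 13-18 fall in the opposite half-year from the baseline, so those contrasts carry the full seasonal difference. Months 7-12 fall in the same half-year.

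The rule also does not clearly date a full-control practice: it has no intervention to initiate, so its month 0 is not defined.

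At stake are the interaction terms, which are the treatment effects. They could be less precise than their standard errors suggest. If start dates differ by arm, they could be shifted.

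**Working it through.** The plan gives no figure for season or for the spread of starts, so there is none to reproduce. The benchmark is the 7-point target difference in section 9.2.

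**Inputs.** From the protocol: 6-month baseline, 18-month intervention, 49 clinics, three two-level factors. Assumed: the prescribing rate follows A·cos(2πt/12), where A is half the peak-to-trough swing, and each month carries equal weight.

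**Step 1: season inside one practice starting at t0.** The mean of this curve over L months is A·cos(π·c/6)·sin(πL/12)/(πL/12), where c is the midpoint of the window. Write S = sin(π·t0/6).

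- Baseline (L = 6, c = t0 − 3): 0.637·A·S
- Months 0-6 (c = t0 + 3): −0.637·A·S, so −1.273·A·S relative to baseline
- Months 7-12 (c = t0 + 9): 0.637·A·S, so 0 relative to baseline
- Months 13-18 (c = t0 + 15): −0.637·A·S, so −1.273·A·S relative to baseline
- All 18 months: −0.212·A·S, so −0.849·A·S relative to baseline

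**Step 2: mean starts s months apart between factor levels.** The largest difference over t0 is the coefficient times A times 2·sin(π·s/12). The last factor is 0.518, 1.000 and 1.414 for s = 1, 2 and 3, so the 18-month contrast shifts by at most 0.44A, 0.85A and 1.20A.

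| Assumed swing (2A) | 18-month contrast, s = 1 / 2 / 3 | Months 0-6 or 13-18 term, s = 1 / 2 / 3 |
|---|---|---|
| 2 points | 0.4 / 0.8 / 1.2 | 0.7 / 1.3 / 1.8 |
| 5 points | 1.1 / 2.1 / 3.0 | 1.6 / 3.2 / 4.5 |
| 10 points | 2.2 / 4.2 / 6.0 | 3.3 / 6.4 / 9.0 |

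These are maxima over the start month. With s = 0 every entry is zero.

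**Step 3: how large a gap chance can produce.** Each main effect compares about 24 with 25 clinics. For starts uniform over W months, the SD of the difference in mean start is (W/√12)·√(1/24 + 1/25) = 0.0825·W. This is 0.5 month for W = 6 and 0.9 month for W = 11. Three months is then 3/0.907 = 3.3 SD even in the wider case.

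**Step 4: starts spread over a year, unrelated to arm.** The months 0-6 contrast of a single clinic has seasonal SD 1.273·A/√2. With a 5-point swing this is 1.273 × 2.5/1.414 = 2.25 points. On a main effect it adds an SD of 2.25 × 0.286 = 0.64 points.

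**Step 5: simulation.** The setting was 49 clinics, no true effect, a 50% baseline rate and a linear difference-in-differences with clinic effects and the protocol's periods, at 200 runs per setting. Monte Carlo error in the type I error is about 1.5 to 3.5 points. The swings simulated were 10 and 20 points, larger than the 5-point case above. Results are for the months 0-6 term.

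Starts spread over 11 months, unrelated to arm (nominal type I error 5%):

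| Visits per provider-month | Swing | Type I error, without → with calendar-month terms | SD of estimate, without → with |
|---|---|---|---|
| 0.67 (16 visits over 24 months) | 10 | 10.0% → 4.5% | 4.76 → 4.27 |
| 0.67 | 20 | 5.5% → 5.0% | 4.42 → 4.02 |
| 5 | 10 | 10.5% → 8.0% | 1.98 → 1.67 |
| 5 | 20 | 23.0% → 4.5% | 3.08 → 1.47 |
| 15 | 10 | 17.0% → 8.0% | 1.48 → 0.97 |
| 15 | 20 | 24.0% → 4.0% | 2.46 → 0.86 |

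Mean bias was within 0.2 points of zero in all of these. At the lowest volume the inflation is not clearly distinguishable from simulation error.

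Intervention-arm starts 2 months later, 5 visits per provider-month: with a 10-point swing the bias was −1.77 points, and −0.09 with calendar-month terms. With a 20-point swing it was −3.30, and −0.05 with them. With a 1-month lag the bias without calendar terms was only −0.01 and 0.17 points. The leak therefore depends heavily on the start month, and the maxima in Step 2 are not expected values.

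**The case against.** The strongest reply is that staggered starts are implied, not stated. The rule in 6.2.2 is a precondition. It would also fit a single launch once every practice is settled, and the schedule in 6.1 shows one timeline. On a common date the problem vanishes. That is correct, and it is why the point is conditional.

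A reader might go further and infer that start dates do differ by arm because only the EHR arms need a build. The documents do not support this:

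- The 5, 7 and 10 months are development times by EHR system, not launch dates. Blocking by clinic organization (9.2.1) largely balances them across arms to the extent that systems follow organizations. Only the pooled remainder clinics weaken this.
- The start rule names enrolment as its trigger, not a build. Under section 4.3 the assigned interventions are described in the educational module, after consent, so disclosure there follows the decision to enrol.
- Six of the eight cells contain an EHR intervention. If builds did delay starts, all clinics with Accountable Justification and about half of those without it would be delayed. The gap between factor levels would be about half the raw delay, so a 1 to 3 month gap needs a raw delay of 2 to 6 months. The same holds for Suggested Alternatives. For Peer Comparison the expected gap is zero.

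A reader might also argue from about six practices per cell that chance imbalance must be large. The model estimates main effects on about 24 and 25 clinics, and chance imbalance adds variance, not bias.

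Finally, the wording on fixed effects need not be exhaustive, and an analysis plan could add a calendar term. Even so, the protocol itself specifies the time terms and promises a contemporaneous comparison that those terms do not secure.

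**Conclusion.** The point holds conditionally. As written, the protocol allows different start dates and specifies a model that cannot adjust for them.

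- **Common launch:** no effect.
- **Different starts, unrelated to arm:** no mean bias, but extra clinic-by-period variation that the listed random effects do not carry. For a 5-point swing and starts spread over a year, the added SD on a main effect's months 0-6 term is about 0.64 points. Combined with the simulated common-launch SD of 1.41 (5 visits per provider-month), this gives √(1.41² + 0.64²) = 1.55, about 10% more.
- **Starts that differ by arm:** for a 5-point swing and a gap of 1 to 3 months, at worst 1.1 to 3.0 points on the 18-month contrast and 1.6 to 4.5 points on the months 0-6 and 13-18 terms. The months 7-12 term is largely unaffected.

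The swing and the stagger are assumptions. The curve is a plain sinusoid on the risk scale with equal monthly weights, and the simulation is linear with clinic effects, so it only approximates the planned mixed logistic model. The documents do not support saying that the trial's estimates are biased. They do support an inexpensive safeguard.

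**What to change.** 1. Add calendar-month fixed effects to the 9.5 model, alongside the period-by-intervention terms. State whether they are by month of year (11 parameters) or by month and year (at least 6 + 18 − 1 = 23). The second also absorbs differences between one winter and the next, and so fits the contemporaneous comparison better. With a common launch those terms replace the period main effects and leave the interactions in place.
2. Define the month-0 date for every practice, including those with no intervention, and say whether it is a common date or the practice's own.
3. Report start dates by arm and by organization.

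**Cost.** Visits must already be dated to be assigned to study months, so no new data are needed. In the simulation at 5 visits per provider-month, adding the terms under a common launch left the SD almost unchanged (1.41 to 1.39, and 1.37 to 1.44). With a 2-month arm lag the SD rose from 1.62 to 1.79 and from 1.47 to 1.70, about 10 to 16%. With starts spread independently of arm it fell.
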